### Intervention description {11a}

All participants will receive usual Army standard care. According to standard Army procedures, all recruits will be taken out of training on confirmation of their injury and referred for extended rehabilitation in a rehabilitation platoon. Recruits may be sent on sick leave, with the duration determined according to the severity of their injury and symptoms. Early rehabilitation will concentrate on upper body, non-impact cardiovascular work and swimming/deep water running. Exercise interventions will aim to maintain cardiovascular fitness using non-impact activities and to maintain strength as pain allows. Once rehabilitation is complete and a recruit is fully fit, they will be graded as fit to return to training. The final functional test before a decision to return to training is made will be the successful completion of a weighted distance march without symptoms, at a level appropriate to the week of training they are returning to. A review by an Army exercise rehabilitation instructor, physiotherapist and general practitioner will be required to determine if a recruit is ready to return to training. The rehabilitation team will be informed of a recruit’s participation in the study, but this will not affect their treatment or rehabilitation programme in any way.

Participants randomly allocated to the intervention arm will receive teriparatide (Terrosa, Gedeon Richter, Budapest, Hungary) in addition to usual Army standard care. Daily subcutaneous injections of teriparatide (20 μg) will be self-administered into the abdomen or thigh using an injection pen and sterile, single use needles. Cartridges of 2.4 mL of a solution containing 600 μg of teriparatide (250 μg/mL) will provide 28 individual fixed doses of 20 μg of teriparatide (20 μg/80 μL solution) when used with a bespoke injection pen. A sharps bin will be provided for the disposal of used needles. Participants will be instructed to store their teriparatide cartridge and injection pen in a refrigerator (2–8 °C). Doses will be reconciled, and a replacement cartridge will be dispensed by the NHS pharmacy every 4 weeks. Daily teriparatide injections will be self-administered for 16 weeks, but where a fracture remains unhealed at week 16, daily injections will continue until week 24. Participants will be given a user manual that fully describes how to use the injection pen and will be trained to use the proper injection technique by investigators. Participants will be instructed to inject at the same time every day. If they forget to inject or are unable to inject at their usual time, participants may take their dose up to 12 h later than planned. When participants are onsite at Infantry Training Centre, Catterick, their teriparatide cartridge and injection pen will be stored by investigators in a temperature monitored refrigerator. When participants are at home there will be no formal temperature monitoring. Participants will be provided with a travel cool pack to transport their teriparatide cartridge and injection pen when travelling between locations.

Participants identified with vitamin D deficiency (serum 25-hydroxyvitamin D < 30 nmol/L [38]) will be treated in accordance with the Ministry of Defence regulation JSP 950, Part 1, Leaflet 2-9-3, irrespective of which arm they have been allocated to. Under the terms of this regulation, to manage vitamin D deficiency, a daily dose of 3200 IU cholecalciferol using cholecalciferol 800 IU (Fultium D_3_/Desunin), or a weekly dose of 60,000 IU (or 20,000 IU on alternate days) using cholecalciferol 20,000 IU capsules will lead to restoration of body stores over 8 to 12 weeks. Long-term maintenance/supplementary therapy is then needed with the equivalent of cholecalciferol 1000 or 2000 IU daily or 10,000 IU weekly.

### Criteria for discontinuing or modifying allocated interventions {11b}

Participants may stop their treatment with teriparatide at any time if they wish. For safety reasons, treatment will be discontinued for individual participants if they experience an unacceptable adverse event or treatment toxicity; an intercurrent illness that prevents further treatment; any change in their condition that in the clinician’s opinion justifies ceasing treatment; or any contraindication to continuing treatment within the summary of product characteristics, including pregnancy [24]. Participants who have their treatment interrupted for 2 weeks or more, intentionally overdose, or exhibit signs of depression (indicated by the C-SSRS completed every 4 weeks prior to teriparatide re-dispensing) will also have their treatment discontinued. Discontinuation of treatment with teriparatide will not be a reason for withdrawal from the study, and participants will complete follow-up visits provided they are willing. Where pre-dose serum calcium is found to be above the upper limit of normal, treatment will be withheld until serum calcium returns to normal and restarted every other day, or every third day according to the clinical judgement of the treating clinician and Chief Investigator. Before restarting treatment, the participant’s correct use of the injection pen will be verified, and differential diagnoses will have been excluded (e.g. primary hyperparathyroidism, excess vitamin D and malignancy). Where pre-dose serum calcium is < 2 mmol/L, treatment will continue with the addition of twice daily calcium (1500 mg) and vitamin D (400 IU) supplementation.

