### Eligibility criteria {10}

Men and women, aged 18–40 years, with single or multiple lower body stress fractures, diagnosed by MRI a maximum of 7 days before date of consent, will be eligible to participate. Potential participants must be undergoing Phase One or Two Army training (i.e. initial or trade training) and will, therefore, have recently passed a physician-screened medical assessment. Eligible participants must provide written informed consent and be able to comply with the study protocol, adhere to study visit requirements, and have baseline safety blood test results within adult reference ranges (analytes listed in Table 1).

**Table 1 Tab1:** Blood and urine biochemistry

		Baseline only	Baseline and weeks 4, 8, 12, 16, 20 and 24
**Blood**	**Safety**	Haemoglobin Platelets White blood cell count Absolute neutrophil count Urate Albumin Bilirubin Alanine aminotransferase Alkaline phosphatase Glucose Parathyroid hormone	Calcium Phosphate Magnesium Sodium Potassium Urea Creatinine High- and low-density lipoproteins Total cholesterol
	**Research**		Parathyroid hormone (including 1-34 and other fragments) Cyclic adenosine monophosphate Vitamin D metabolites Bone remodelling compounds: Carboxyl-terminal collagen cross-links Procollagen type 1 N-terminal propeptide Sclerostin Osteoprotegerin Receptor activator of nuclear factor kappa-B ligand Dickkopf-related protein 1 Fibroblast growth factor 23 Butyrate
**Urine**	**Safety**		Calcium Phosphate
	**Research**		Pyridinoline Deoxypyridinoline Oxalate Cyclic adenosine monophosphate

Additional bone remodelling compounds may be analysed if assay methodologies are validated during the trial

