#### Exploratory outcomes

##### Blood and urine biochemistry

Blood and urine samples will be collected at baseline and weeks 4, 8, 12 and 16. Where a fracture remains unhealed at week 16, additional blood and urine samples will be collected at weeks 20 and 24. Venous blood samples will be collected from an antecubital vein. The NHS institution laboratory will analyse blood and urine samples for safety (Table 1). Aliquots of serum, plasma and urine will be stored at − 80 °C, before being defrosted prior to research analyses (Table 1). Analytes will be analysed as a change from baseline. All blood and urine biochemical analyses will be completed by technicians blind to the randomisation outcome.

Slight and transient elevations of serum calcium concentration are normal following the injection of teriparatide. It takes 4–6 h for serum calcium to reach C_max_ and 16–24 h to return to baseline after each dose [24]. Therefore, blood samples will be collected at least 16 h after a participant’s most recent teriparatide injection. Where their regular dosing regimen means treatment would be interrupted to comply with this, the time of their last dose will be recorded. In the event of a hypercalcemia result, a trough measurement will be made within 7 days, before any dose modifications or discontinuations are made. Randomisation will be permitted prior to the receipt of baseline plasma parathyroid hormone concentration. However, in the unlikely event of a participant presenting with a plasma parathyroid hormone concentration outside the adult reference range, they will be called back for review and instructed to stop injecting teriparatide.

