### Safety

One safety concern associated with teriparatide during its development was the possible association with osteosarcoma, due to a preclinical animal study reporting a dose-dependent increase in the incidence of osteosarcoma and some other rare bone tumours in one breed of rat, treated with near life time, high doses of teriparatide [25]. This finding was not observed in subsequent animal studies with other animal models or breeds of rat, and treatment with teriparatide in humans has been demonstrated to be safe, with no association between teriparatide and osteosarcoma observed since surveillance studies commenced in 2003 and 2009 [24–26]. The maximum total duration of treatment with teriparatide was increased from 18 to 24 months by the European Medicines Agency and US Food and Drug Administration based on safety data and post-marketing experience [51, 52].

For safety, participants’ blood and urine samples, collected at baseline and every 4 weeks throughout the study, will be analysed to ensure they are within adult reference ranges (analytes listed in Table 1). Hypercalcaemia and hypercholesterolaemia have been reported in individuals treated with teriparatide [24]; hence, serum calcium and total cholesterol will be monitored throughout the study. Teriparatide may cause small increases in urinary calcium excretion [24]; thus, participants’ urine calcium will be monitored. Participants will be expected to be otherwise healthy because in order to be undergoing Army training, they will have recently passed a physician screened medical assessment.

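### Two sections give different first actions for the same high serum calcium result, and neither refers to the other

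*Protocol article*

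**What the plan says.** Two places in the protocol article prescribe what follows a raised serum calcium.

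- **Criteria for discontinuing or modifying allocated interventions {11b}.** "Where pre-dose serum calcium is found to be above the upper limit of normal, treatment will be withheld until serum calcium returns to normal". Treatment is then "restarted every other day, or every third day according to the clinical judgement of the treating clinician and Chief Investigator". Before restart, correct use of the pen is checked and "differential diagnoses will have been excluded". The same section stops treatment for "Participants who have their treatment interrupted for 2 weeks or more".
- **Exploratory outcomes, Blood and urine biochemistry.** "In the event of a hypercalcemia result, a trough measurement will be made within 7 days, before any dose modifications or discontinuations are made". It also sets the timing of routine samples: "blood samples will be collected at least 16 h after a participant’s most recent teriparatide injection". Where that timing would interrupt a participant's regular dosing, the time of the last dose is recorded instead. The section gives 16 to 24 h for calcium to return to baseline after a dose.

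Safety calcium is scheduled in Table 1 at "Baseline and weeks 4, 8, 12, 16, 20 and 24". The Safety part of the Discussion likewise describes samples "collected at baseline and every 4 weeks throughout the study".

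**The concern.** Both sections state a rule for a high calcium result, so this is not a detail left to another document. One rule holds treatment on the result. The other forbids any change to dosing until a further measurement has been made. Neither section cites the other, and *pre-dose* is not defined.

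If both rules apply to the same result, two members of staff could handle the same participant in opposite ways and each be following the protocol. One participant would go on injecting daily with an unresolved high result; another would be held. Hypercalcaemia is an effect that the protocol itself says has been reported with teriparatide, so the situation is foreseeable.

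**Working it through.** There is no sample size, power or error-rate figure to reproduce. The check sets the two rules side by side and counts doses.

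**Inputs**

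- Dosing: 20 μg once daily (Intervention description {11a}).
- Routine sample: at least 16 h after the last injection (Blood and urine biochemistry).
- Repeat trough: within 7 days (Blood and urine biochemistry).
- Interruption limit: 2 weeks = 14 days ({11b}).
- Scheduled safety calcium: every 4 weeks = 28 days (Table 1; Safety).

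**Step 1. Is a routine sample already pre-dose?** With injections about 24 h apart, a sample that meets the 16 h rule and is drawn before the next injection falls in the last 24 − 16 = 8 h of the dosing interval. It is a pre-dose sample in the ordinary sense. The exception is a sample accepted with only the dose time recorded, which may be earlier than 16 h.

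**Step 2. Does {11b} reserve *pre-dose* for a confirmatory sample?** Nothing in it says so. The same section uses the same term for its rule on calcium below 2 mmol/L, and that rule involves no confirmatory trough. This favours reading the term as covering ordinary routine samples.

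**Step 3. Apply both rules to one high result**

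| Sample | {11b} | Blood and urine biochemistry | Compatible? |
|---|---|---|---|
| At least 16 h after dose, before the next dose (the usual case) | Withhold | No dose change until trough, within 7 days | Not as written |
| Under 16 h after dose (the exception) | Not triggered, if the sample is not pre-dose | Obtain trough first | Yes: trough, then {11b} acts on it |

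A hold is reasonably counted as a dose modification, since it is set out under the heading on discontinuing or modifying the intervention.

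**Step 4. Size until the repeat.** The difference is the number of daily injections given under one rule and withheld under the other:

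- trough before the next injection: 0 × 20 μg = 0 μg;
- trough at the full 7 days: 7 × 20 μg = 140 μg.

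The range is therefore 0 to 7 doses per affected participant. Dosing could diverge further after the repeat, because {11b} restarts at a lower frequency and the biochemistry section does not say what follows a normal trough. The documents give no basis for putting a figure on that.

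**Step 5. The 2-week clause.** A hold shorter than 14 days can end in restart; one of 14 days or more ends in discontinuation. The two clauses are compatible. What the text does not say is whether a hold directed by the protocol, including time spent excluding other diagnoses, counts as an interruption under that clause.

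**The case against.** The strongest reply is that the rules run in sequence. The biochemistry section starts from any hypercalcaemia result, requires a trough, and only then allows a change; {11b} then acts on that trough as its pre-dose value. The delay makes sense, because calcium may still be returning to baseline at 16 h, and some samples are accepted earlier than that. Also, {11b} does not say that the hold is immediate.

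Much of this stands. The sequence is a possible reading, so this is an ambiguity that can be resolved and not an unavoidable contradiction. But the sequence is not stated, and it does not fit easily with the usual routine sample, which is already pre-dose (Steps 1 and 2).

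A reader might go further and infer that restart is blocked, since the next scheduled calcium is 28 days away and the interruption limit is 14. The documents do not support this:

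- the biochemistry section itself provides an off-schedule test within 7 days;
- the adverse event section {22} counts abnormal laboratory results as adverse events and follows all events until they resolve;
- the retention section {18b} makes 4-weekly contact a minimum, with contact as often as daily for participants on site.

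It is also fair to say that this article condenses a fuller protocol, and that retest logistics commonly sit in working instructions. That answers a complaint about missing detail. It does not answer a difference between two rules that the article states.

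**Conclusion.** The concern holds as a minor point of participant safety and consistent dosing. For a high calcium result in a routine pre-dose sample, the two sections give different first actions, differing by up to 7 daily doses (140 μg) before the repeat. This rests on two assumptions: that a compliant routine sample counts as pre-dose, and that a hold counts as a dose modification. Both are the more natural readings, but neither is spelled out.

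A reader might infer a large loss of exposure within the 8-week primary window. For a week 4 result, 56 planned doses would become 28 + 28/2 = 42, 28 + 28/3 ≈ 37, or 28 if treatment stopped: a cut of 25% to 50%. That should not be claimed. The first two figures assume a hold of no length, the third assumes discontinuation, and all three describe a single participant. The number affected is not stated, and eligibility requires baseline safety bloods within reference ranges and excludes pre-existing hypercalcaemia. A diluted treatment contrast is therefore not shown. The primary analysis is by intention to treat regardless of compliance, and its validity is not in question.

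**What to change.** Reconcile {11b} and the biochemistry section into one ordered rule, placed in one section and cross-referenced from the other. It should state:

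1. which sample triggers action, defined by its time since the last injection;
2. what happens to dosing while the repeat measurement is awaited;
3. how a protocol-directed hold, and the time spent excluding other diagnoses, relates to the 2-week interruption clause.

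The clinical content of each item is for the sponsor's medical lead; this review takes no view on which rule is right.

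The cost is a short amendment to the protocol, with matching working instructions, taken through the approvals listed in section {25}. It needs no change to the sample size or the analysis. The 4-weekly diary review already captures reasons for missed doses ({11c}), so protocol-directed holds can be identified without new data collection.

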### Strategies to improve adherence to interventions {11c}

Face-to-face reminders about how and when to inject teriparatide, how to store teriparatide, and what to do in the event of a missed dose will take place when the drug is initially dispensed, each time the drug is re-dispensed, and during each study visit. Participants will record self-administration of teriparatide in a daily diary. Diaries will be reviewed by investigators every 4 weeks, alongside any problems that participants might be having with injections, and the reasons for any missed doses. Used teriparatide cartridges will be collected from participants every 4 weeks, with the number of unused doses recorded to monitor adherence to the intervention.

### Relevant concomitant care permitted or prohibited during the trial {11d}

The use of medication bought over the counter or prescribed by other healthcare professionals will be permitted, except for non-steroidal anti-inflammatory drugs and vitamin D or its analogues. Participants’ use of analgesics will be recorded throughout the study using their participant diary. The combined use of teriparatide and cardiac glycosides (e.g. digoxin or digitoxin) may predispose participants to digitalis toxicity [24]; thus, participants required to begin taking cardiac glycosides will be withdrawn from the study. Participants required to begin taking medications that affect serum calcium (including but not limited to lithium, thiazides or alendronic acid) will also be withdrawn from the study.

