
### Plans to promote participant retention and complete follow-up {18b}

Investigators will maintain regular contact with participants throughout their participation in the trial to offer support as required. Participants will be asked for their preference with regards to the form this will take (i.e. telephone or video calls, text messages, emails, face-to-face consultations). All participants will meet with investigators a minimum of every 4 weeks. Participants who remain onsite at Infantry Training Centre, Catterick will meet with investigators as frequently as every day. Study visits will be scheduled to avoid disruption to each participant’s rehabilitation programme, with the aim to incorporate the trial into routine life within their barracks. Participants who discontinue or deviate from their allocated intervention protocol will remain in the trial for all follow-up visits, provided they are willing. For participants who withdraw or are withdrawn from the study, all data collected up to the date of withdrawal will be retained for use in the study. The reason for withdrawal, if given, and loss to follow-up will be recorded.

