## Statistical methods

### Statistical methods for primary and secondary outcomes {20a}

A full statistical analysis plan (SAP) will be developed by the Trial Statistician and Chief Investigator before the final data lock and will be submitted to the independent Data Monitoring Committee (DMC) and Trial Steering Committee (TSC) for approval [48]. The primary efficacy analysis will be based on the intention-to-treat principle in which all participants will be analysed according to the trial arm to which they were allocated, regardless of compliance. The primary outcome (radiological healing by two Fredericson grades or more, or reduction in grade to zero, 8 weeks after randomisation) will be analysed using a logistic regression model. This model will include the baseline stratification variables (vitamin D status and single or multiple lower body stress fractures); anatomical site of fracture; baseline MRI grade; allocated trial arm; and any other baseline prognostic variables pre-specified in the SAP. The estimate of efficacy will be the between group difference from the analytical model, calculated with 95% confidence intervals and with statistical significance set at the 5% level (two-sided). Secondary outcomes will be analysed in an analogous manner, i.e. using appropriate statistical models with stratification variables, additional specific prognostic variables (including the baseline value of the outcome where available) and allocated trial arm. A secondary analysis of MRI grading at each time point using a logistic regression model with a generalised estimating equation approach to parameter estimation and a specified auto-regressive correlation structure, i.e. to allow for the correlation in outcome between timepoints, will also be completed.

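### Participants who start a cardiac glycoside or a drug affecting serum calcium are withdrawn from the study in either arm, when stopping teriparatide and keeping follow-up would be enough

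*Protocol article*

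**What the plan says.** Section {11d} (concomitant care) has two withdrawal rules. The first says "participants required to begin taking cardiac glycosides will be withdrawn from the study", and the reason given is "The combined use of teriparatide and cardiac glycosides" and the resulting risk of digitalis toxicity. The second says that participants who must start "medications that affect serum calcium (including but not limited to lithium, thiazides or alendronic acid) will also be withdrawn from the study"; no reason is given. Both refer to participants in general.

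Other sections treat similar events differently:

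- Section {11b} stops teriparatide for "any contraindication to continuing treatment within the summary of product characteristics, including pregnancy", and also for toxicity, intentional overdose or signs of depression. It then says "Discontinuation of treatment with teriparatide will not be a reason for withdrawal from the study", with follow-up visits continuing if the participant is willing.
- Section {18b} says "Participants who discontinue or deviate from their allocated intervention protocol will remain in the trial for all follow-up visits", again subject to willingness. It treats withdrawal as a separate status: "For participants who withdraw or are withdrawn from the study, all data collected up to the date of withdrawal will be retained".
- Section {20a} sets an intention-to-treat primary analysis in which "all participants will be analysed according to the trial arm to which they were allocated, regardless of compliance".
- Section {20c} describes participants with no primary outcome as excluded from the primary analysis. Imputation is a sensitivity analysis, to be done if judged appropriate.

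**The concern.** The article distinguishes stopping study drug from leaving the study, so the wording in {11d} cannot be put down to loose shorthand. A site that follows it would end follow-up for a participant whose outcomes could still be measured.

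The stated hazard with glycosides comes from combining them with teriparatide. Stopping teriparatide removes that combination, and under {6b} controls receive standard care only. Ending follow-up adds no protection in either arm.

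What is lost is outcome data after randomisation, and a protocol rule causes the loss. Withdrawal before week 8 loses the primary outcome. Later withdrawal truncates time to radiological healing and time to clinical healing, and brings forward the end of adverse event recording. The missingness may also be informative: a participant started on alendronic acid, for instance, may have a bone problem that bears on healing.

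**Working it through.** **1. The rules side by side**

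| Event after randomisation | Section | Teriparatide | Follow-up |
|---|---|---|---|
| Toxicity, label contraindication, pregnancy, intentional overdose, signs of depression | {11b} | stopped | continues if willing |
| Other discontinuation of, or deviation from, the allocated intervention | {18b} | – | continues if willing |
| Starts a cardiac glycoside | {11d} | ends with withdrawal | ends, either arm as written |
| Starts a drug affecting serum calcium | {11d} | ends with withdrawal | ends, either arm as written |

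For withdrawn participants, {18b} provides for keeping data up to the withdrawal date. Nothing in the article provides for collecting outcomes after it. Under {20c} a missing week 8 outcome then means exclusion from the primary analysis.

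**2. The plan's sample size, reproduced**

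Inputs from {14}: success 43% (control) and 71% (intervention), two-sided 5%, 80% power, continuity-adjusted chi-squared test, 20% drop-out by week 8, 68 randomised and 54 evaluable per arm.

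With p̄ = (0.43 + 0.71)/2 = 0.57 and d = 0.28:

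- Uncorrected: n = [1.960·√(2·0.57·0.43) + 0.842·√(0.43·0.57 + 0.71·0.29)]² / 0.28² = 47.9 per arm.
- Continuity-corrected: n′ = (n/4)·[1 + √(1 + 4/(n·d))]² = 54.8 per arm, against 54 stated.
- Drop-out: 54/0.80 = 67.5, rounded up to 68 per arm, 136 in total.

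Power with n per arm is Φ{[d − 1/n − 1.960·√(2p̄(1−p̄)/n)] / √[(0.43·0.57 + 0.71·0.29)/n]}. At n = 54 this is Φ(0.0747/0.0914) = Φ(0.818) = 79.3%. The plan's figure reproduces to within a point and is not in dispute.

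**3. Scale of an extra loss**

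The article gives no rate of starting these drugs, so the number of outcomes lost cannot be calculated. The range of 1 to 5 is an assumption. The formula uses n = N/2.

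| Evaluable at week 8 (N) | Losses beyond the 20% | Power |
|---|---|---|
| 108 | 0 | 79.3% |
| 107 | 1 | 78.9% |
| 106 | 2 | 78.4% |
| 105 | 3 | 78.0% |
| 104 | 4 | 77.5% |
| 103 | 5 | 77.1% |

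That is about 0.4–0.5 points per participant. The allowance is 68 − 54 = 14 per arm, and losses within it cost nothing against plan.

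Each unobserved outcome could have been a success or a failure, so it widens the best-to-worst-case range of that arm's success rate by 1/68 = 1.5 percentage points. Five in one arm give 5/68 = 7.4 points.

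**The case against.** The strongest objection is that the rule will rarely be triggered. Participants are aged 18–40, have recently passed a medical assessment and have baseline safety bloods in range. Section {10} excludes hypercalcaemia, severe renal impairment, metabolic bone disease, depression on the C-SSRS and current digoxin. This stands: the number affected is probably small, and the figures above give a scale, not a forecast.

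Section {11d} could also be read as a specific exception to a general rule, since {18b} recognises participants withdrawn by the trial. That makes it less than a logical contradiction, but an exception that loses outcomes still needs a reason, and safety does not supply one. Because the glycoside sentence opens with the combination with teriparatide, it might be meant for that arm only. The text does not say so, and the serum calcium sentence gives no such cue.

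A third argument is that these drugs could interfere with the evaluation of teriparatide, which is an exclusion ground at entry. After randomisation, under intention to treat, that does not justify ending observation. An analysis that sets such participants aside remains possible if their data exist.

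Some of the loss is softened. Adverse events are recorded for 4 weeks after participation and followed to resolution. Time to discharge comes from Army records. Section {20c} plans a comparison of included with excluded participants and possible imputation. None of this recovers a week 8 MRI that was never taken. The full protocol may define levels of withdrawal, but the article as published states withdrawal from the study.

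**Conclusion.** The concern holds. As written, {11d} creates avoidable missing outcomes in both arms, is out of line with {11b} and {18b}, and works against the intention-to-treat analysis in {20a}. It gives no safety gain over stopping teriparatide.

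The expected effect is small and cannot be quantified from the article. If one to five extra participants were lost before week 8 beyond the planned 20% (an assumed range), power would fall from 79.3% to between 78.9% and 77.1%. If all were in one arm, the best-to-worst-case range of its success rate would widen by 1.5 to 7.4 points. The case for change rests on avoidable missing data and a cheap remedy, not on power.

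**What to change.** In both sentences of {11d}, replace withdrawal from the study with: *will discontinue teriparatide (if allocated) and remain in follow-up for all outcomes, provided they are willing*. The explicit trigger that separates teriparatide from these drugs stays.

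An optional clarification would exempt the vitamin D treatment in {11a} and the calcium and vitamin D supplementation in {11b}. The list of drugs affecting serum calcium is open-ended and, read literally, could catch treatments that the protocol itself prescribes.

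The cost is one minor amendment through the route in {25}: agreement by the Trial Management Group, then approval by the research ethics committee, the MHRA and the Health Research Authority, and acceptance by sites. The follow-up schedule already exists, so no new visits are needed. The trial status section says approval to widen recruitment will be sought, and this change could be submitted with it.
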